## Methodology

### Trial design

This study will be an open-label, multicenter RCT involving adult patients with drug-susceptible TB randomized (1:1 ratio) to either the intervention (adherence and appointment reminders, health messages, and 24-h health care worker call service) or control arm. The study will have nested qualitative and economic evaluation sub-studies and a process evaluation to determine the uptake and use of the intervention.

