#### Exclusion criteria

Inability to use a basic feature phone or presence of a clinical condition that interferes with appropriate use of the mobile phone for voice calls (e.g., deafness, severe cognitive impairment)Ongoing participation in another interventional study that the investigator believes will interfere with study procedures or assessment of the outcomes of this study.Patients who are critically ill.Patients with drug-resistant TB (Rifampicin resistant, Multi-drug resistant, and extensive drug-resistant TB).Patients with TB meningitis or osteoarticular TB.Any other clinical condition that, in the opinion of the site investigator, would make the participant unsuitable for the study or unable to comply with dosing requirements.

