### Randomization, blinding, and allocation concealment

At baseline, participants will be randomly assigned (1:1 ratio) to either the intervention or control arms (Fig. 2). The study statistician generated study allocation slips for participants for each study site using and these are then enclosed in sealed opaque envelopes. The number of cards allocated per study site will be equal to the enrolment target assigned to the study site. The allocation slips will indicate either the intervention or the control arm. The study arm will be allocated by drawing one envelope by a participant from a closed envelope box. Patients will randomly pick and open an envelope and they will be allocated a study arm that is indicated on the enclosed card. Since the opaque envelopes will be used and drawn from a closed opaque box, the allocation sequence is concealed from the recruiting study staff. We will maintain screening and enrolment logs at each study site to ensure that there is no bias in randomization and enrolment. Due to the study design involving voice reminders to participants, it is not possible to blind participants. However, the analyzing statistician will be blinded to the allocated arms.

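### Opaque envelopes do not conceal the last assignments from a site box that holds only as many cards as the site's enrolment target

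*Protocol article*

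**What the plan says.** All the elements stand in the protocol article.

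- **Ratio** (Randomization, blinding, and allocation concealment): "participants will be randomly assigned (1:1 ratio) to either the intervention or control arms".
- **Box size** (same section): the statistician prepares slips site by site, and "The number of cards allocated per study site will be equal to the enrolment target assigned to the study site".
- **Draw** (same section): "The study arm will be allocated by drawing one envelope by a participant from a closed envelope box", and "Patients will randomly pick and open an envelope and they will be allocated a study arm that is indicated on the enclosed card".
- **Conclusion drawn** (same section): because envelopes and box are opaque, "the allocation sequence is concealed from the recruiting study staff".
- **Safeguard named** (same section): "We will maintain screening and enrolment logs at each study site to ensure that there is no bias in randomization and enrolment".
- **Blinding** (Trial design): "This study will be an open-label, multicenter RCT".
- **Discretion over entry** (Exclusion criteria): "Any other clinical condition that, in the opinion of the site investigator, would make the participant unsuitable for the study", or unable to comply with dosing.

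The article mentions no surplus cards, no topping up, no return of drawn envelopes, no central release of assignments and no masking of the box total.

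**The concern.** Concealment means that whoever decides on entry cannot foresee the next assignment. An opaque envelope in an opaque box keeps the individual card hidden. It does not hide the composition of a finite box whose size and ratio are known. Each opened card removes one from a known total, and in an open-label trial the arm of each earlier participant is visible at the site. Target minus tally then gives the cards left in each arm. The odds drift away from 1:1 as the box empties. Once one arm is used up, every later assignment is fixed, and the last card is always known.

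This happens even when each draw is done honestly. What is at stake is selection at entry: someone who expects a particular arm could defer a patient, or use the investigator-opinion exclusion, on grounds close to adherence, retention and treatment success.

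**Working it through.** **Inputs from the protocol article.** Total 274, 137 per arm (Sample size determination); five sites (Abstract); 1:1 allocation; cards per site equal to the site target. Monthly intake is 25, 9 and 24 at the three original sites (Study settings), and 13 and 10 at the two added sites (Recruitment of study participants; Study settings gives about 12 each).

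**Assumptions.** Site targets are not given, so two splits of 274 are used: near-equal (54, 54, 54, 56, 56) and proportional to intake (84, 30, 82, 44, 34). Each box is taken to hold *m* cards per arm, drawn without replacement. Staff are taken to know the target and keep a tally.

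**The plan's own figure.** The total of 274 can be reproduced. The control rate is not stated. With 70% versus 85% assumed, two-sided 0.05, power 0.80 and pooled variance, *n* = 120.5 per arm, and 120.5/0.882 = 136.6, so 137 per arm. This confirms the total number of cards and has no other bearing on the point.

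**Assignments known with certainty.** For a box of 2*m* cards drawn to its end, the expected number is 2*m*/(*m*+1).

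- *m* = 27: 54/28 = 1.93 per site.
- Near-equal split: 3 × 1.93 + 2 × (56/29 = 1.93) = 9.6 of 274, or 3.5%.
- Intake split: simulation gives 9.6, again 3.5%.
- In a 54-card box, the chance that at least the last two draws are certain is 26/53 = 49%. For at least three it is 26/53 × 25/52 = 24%.

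The total hardly depends on the split, because the expectation is close to 2 for any plausible site size.

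**Accuracy of the best guess.** Always naming the arm with more cards left is right in an expected share of [*m* + ½(4^*m*/C(2*m*,*m*) − 1)]/(2*m*). For *m* = 27, 4^27/C(54,27) = 9.25, so the share is (27 + 4.13)/54 = 57.6%. Over all sites it is 57.6% (near-equal) and 57.4% (intake), against 50% for independent assignment. Over the last 10 draws of a 54-card box it is about 70%.

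**Odds of 2:1 or better.** By simulation, about 37 assignments (near-equal) and 36 (intake), that is 36 to 38 across runs, or 13-14% of 274. Within these the better guess is right about 79% of the time.

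**If boxes are not emptied.** Suppose the three original boxes were sized to share all 274, the two added sites have boxes equal to their own share, and enrolment follows either five-site split. Simulation then gives about 3.8 certain assignments (1.4%), about 15 at 2:1 or better (5.5%) and 55% correct guesses.

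**After the change.** With each box twice the target: no certain assignments, fewer than 0.1 at 2:1 or better over the whole trial, and 52% correct guesses. The variance of one arm's count at a site of target *n* is *n* × ¼ × *n*/(2*n* − 1). For *n* = 54 this is 54 × 0.25 × 54/107 = 6.81, SD 2.6. Over five sites the SD is about 5.9, and for the difference between arms about 11.8. A difference of 12 keeps 1 − (12/274)² = 99.8% of the efficiency of exact balance.

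**The case against.** **Unstated premises.** The article does not say that recruiters know the site target, that each box is split exactly equally, or that drawn cards stay out. It says logs are kept at each site, not that recruiters hold them or count arms from them. This stands: the prediction is conditional on these premises. They are the natural reading of a card count equal to the target with 1:1 allocation, but they are inferred.

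**Emptied boxes.** The main figures assume that all five boxes are drawn out. Two sites were added under protocol version 2.0 (Protocol amendments), and the article does not say whether the original boxes were resized. This stands too, so the figures are an upper bound.

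**Low predictability for a balanced design.** The same formula gives 70.8% correct for known blocks of 4 and 66.6% for known blocks of 8. A single large box is therefore among the less predictable ways to force 1:1 within a site. True, but it does not make the concealment sentence correct, and a cheap change takes most of the remaining predictability away.

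**Effect on the result.** A reader might infer that treatment success will be materially biased. The documents do not support that: nothing indicates that anyone used the information. As a deliberate extreme, suppose every draw at 2:1 or better is acted on and expected success shifts by 10 points up or down (an assumption). The bias is about 0.137 × (0.79 − 0.21) × 20 = 1.6 points. Acting on certain draws alone gives 0.035 × 20 = 0.7. The planned difference is 15 points.

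**Existing safeguards.** Screening and written consent already precede participation (Ethical considerations), and logs may expose late exclusions afterwards. They do not prevent prediction or deferral.

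**Conclusion.** The statement that allocation is concealed from recruiting staff is too strong for a small, late share of draws at each site. The upper bound is about 10 of 274 assignments (3.5%) certain, 36 to 38 (13-14%) predictable at 2:1 or better, and 57-58% correct guesses overall. In the scenario where the original sites stop short of emptying their boxes, this falls to about 1.4%, 5.5% and 55%. The figures rest on assumed site targets, an equal split in each box, drawing without replacement, and staff who know the target and tally draws.

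A reader might go further and conclude that staff certainly hold the exact remaining counts, or that concealment fails throughout recruitment. Neither follows: staff knowledge is not documented, and in the early and middle part of a large box the odds stay close to even. Discretionary exclusion offers a route to selection bias, but its size is not shown. The point is worth correcting because the correction is cheap.

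**What to change.** In Randomization, blinding, and allocation concealment, replace the sentence that equates the number of cards with the site target. State instead that each site's box holds clearly more 1:1 cards than the target, for example about twice as many, and that the number is known only to the study statistician. Alternatively, issue assignments from a statistician-held list that runs past the target.

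For boxes in use, the statistician adds an undisclosed number of sealed cards, equal for each arm. At the reported status 123 of 274 were enrolled (Trial status), so the most predictable stretch probably still lay ahead at most sites.

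The cost is extra cards, one changed sentence and a slight loss of exact balance: an SD of about 2.6 for one arm's count at a 54-patient site and about 6 of 274 overall, so about 12 for the difference between arms. The effect on power is negligible.

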### Participant follow-up, procedures, and timelines

Participant follow-up before six months, the total study duration is 24 months, and participants will have evaluations at baseline and months 2, 5, and 6, consistent with the Ministry of Health visit scheduling for patients with TB (Table 1). At each visit, the participants will be given their future appointment dates.

**Table 1 Tab1:** Study timelines and procedures

Study procedures	Study procedure completed							
Month	0	0	2	2	5	5	6	6
Study arm	I	C	I	C	I	C	I	C
Screening	**√**	**√**						
Informed consent	**√**	**√**						
Physical evaluations and interviews	**√**	**√**	**√**	**√**	**√**	**√**	**√**	**√**
Demographic and socio-economic questionnaire	**√**	**√**	**√**	**√**	**√**	**√**	**√**	**√**
Sputum GeneXpert^*^	**√**	**√**			**√**	**√**	**√**	**√**
Drug culture and susceptibility tests^β^	**√**^β^	**√**^β^	**√**^β^	**√**^β^	**√**	**√**	**√**^β^	**√**^β^
Cost-effectiveness questionnaire	**√**	**√**	**√**	**√**	**√**	**√**	**√**	**√**
Qualitative assessment	**√**	**√**	**√**	**√**			**√**	**√**

Note: I-Intervention arm, C-control arm

^*^Additional tests to ascertain sputum conversion may be added at the discretion of the investigator.

^β^Drug susceptibility testing will be done in-line with national TB guidelines. Sputum cultures may be done at 2 months to ascertain sputum conversion and sputum for genotyping TB stored.

**√** indicates procedure completed at the indicated timeline

### Participant withdrawal and post-trial care

Participants can be withdrawn from the RCT at their request, following death or disengagement from care. Participants may also be withdrawn at the discretion of the investigator for safety concerns. If the subject withdraws from the RCT, the study staff will not perform further evaluations, and data collection will cease. The RCT will retain data collected before withdrawal unless the participant requests otherwise. Study staff will track participants who miss visits. If a participant does not attend for two consecutive months, they will be considered lost to follow-up (attrition). All withdrawn participants will be linked to the standard of care. Participants with cured TB will be exited from care while those with no evidence of cure will be linked to tertiary TB services at their treatment facilities. At the end of the RCT, participants will have their treatment details updated in the TB register and are discharged from care.

### Data collection and management

We will comply with the Ugandan laws on data privacy and management [45]. Data will be entered using REDcap [46]. The system automatically flags missing and out-of-range values, which will be attended to by the RCT staff.

### Data collection

At baseline, the staff will obtain sociodemographic data (age, sex, marital status, level of education, employment status, income, transport costs, distance from the facility) and data on TB infection (method of diagnosis, site of infection, and rifampicin resistance at baseline). Prospectively, data will be obtained on adherence, symptoms, sputum tests, missed appointments, and clinic visits (Table 1). Participants will also be interviewed on phone call costs, hospitalization, and over-the-counter treatments. At baseline, we will interview patients (qualitative data) on their anticipated challenges in the use of IVRT and anticipated benefits and challenges. At months 2 and 6, qualitative data will be collected on acceptability and experience with the digital intervention. We will determine the sputum conversion rate at 2 months and cure at 6 months. Chest radiographs will be used to determine the cure for patients with clinical TB. TB cards and treatment registers will be reviewed for death, adherence, and date of patient visits. We will use micro-costing to obtain data on the direct and indirect costs.

### Trial endpoints

The primary endpoint is treatment success (at 6 months): treatment success is a composite outcome, comprising treatment completion and cure in patients with clinically and bacteriologically diagnosed TB, respectively. It is a robust and agreed indicator of treatment success in TB programs. In patients with bacteriologically diagnosed TB, cure is defined as having a negative sputum test in the last month of treatment and on at least one previous occasion [47]. For clinically diagnosed patients, completion entails 6 months of therapy. The denominator for each arm will be the number of patients enrolled. At the same time, the numerator is the sum of bacteriologically and clinically diagnosed patients with cure or treatment completion, respectively.

This RCT also has several secondary endpoints. First, we will determine the TB cure rates in patients with microbiologically diagnosed TB. Second, we will determine treatment completion for patients clinically diagnosed with TB in the two arms: Third, retention rates will be determined and compared between the study arms. Patients will be deemed to be actively engaged in care if they attend a clinic visit within one month of a scheduled appointment. Additionally, we will compare appointments. We will categorize visits as “early,” if they present before an appointment, “prompt” if they show up within three days after the appointment date, “late” if they present after three days but within 30 days of a scheduled appointment and missed if patients do not show up at all or present after 30 days. Fourth, we will determine the incremental costs per additional DALY averted per percentage point increase in treatment success in the intervention versus the control arm. In addition, we will compare adherence rates at months 2 and 6. Depending on the availability of drug susceptibility tests, we will compare the rates of MDR-TB. To understand the impact of the intervention on the treatment outcomes and the potential for adoption and scaling of the intervention, we will explore the perceptions and experiences of patients and care providers towards the MHI. Finally, we will determine the uptake and adherence to the intervention. We will consider the successful receipt of a reminder as a proxy for the utilization of the technology. Therefore, we will determine the proportion of successful calls in the intervention and control arms.

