### Study settings

To ensure the generalizability of the results of this study, we planned to enroll patients from several facilities that are representative of typical TB facilities in Uganda. Most patients with tuberculosis [37, 38] are treated at low-level public facilities but a significant burden also exists in urban settings [37, 38]. Therefore, we selected both public and rural TB treatment facilities. Kisenyi Health Center, the first study site, is a large public health center situated within the oldest slum in Kampala which is home to over 23,000 people vulnerable to TB. As a result, the facility receives about 25 new TB patients per month. In addition, Kiryandongo is a rural agrarian district hospital that serves 266,000 people, including 50,000 refugees. The hospital registers an average of 9 new TB cases per month. In contrast, Kasangati Health Center IV is a busy peri-urban facility that serves the Kyadondo East in the Wakiso district and attends to approximately 24 new TB cases per month. To expedite participant accrual, two additional facilities were added to the study protocol version 2.0. Bweyogerere and Kawanda Health Centre IIIs are in the Wakiso district and serve a peri-urban population. They treat approximately 12 patients with TB each per month.

At all health facilities [39, 40], patients with at least one of the dangerous symptoms of TB are offered a sputum GeneXpert test while those unable to expectorate are offered alternative diagnostic tests (CXR, TB LAM, sonography, tissue biopsy, CSF analysis, etc.). Patients with sputum-positive TB are then tested for rifampicin resistance using the GeneXpert MTB Rif assay [40].

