#### Inclusion criteria

Evidence of TB diagnosis either confirmed bacteriologically by Xpert MTB/RIF Version G4 assay (Cepheid, Sunnyvale, CA, USA) or clinically diagnosed.Evidence of a personally signed and dated informed consent document that indicates that the participant (or a legal representative) has been informed of all pertinent aspects of the study.Willingness to comply with scheduled visits, treatment plans, laboratory tests, and other study procedures.Aged ≥ 18 yearsMobile phone ownership. Subject to funding, study participants without mobile phones may be provided with mobile phones.Patients who can understand Luganda, Runyankore, Swahili, or English. These languages are the languages spoken by most patients at the study health facilities. If we add Lira RRH as a study site, we will add Luo, the predominant language spoken in the Lango region. Other languages may be added to the service if the anticipated demand surpasses 30 patients.

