### Sensitivity analysis

To determine the impact of nonadherence to the study intervention, we will stratify the analysis by utilization of the CFL-TB tool. For both primary and secondary quantitative endpoints, we will conduct an overall and stratified analysis by HIV status, TB type (pulmonary versus other forms of TB), and gender.

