## Discussion

This study is a multicenter, open-label, randomized controlled trial to determine the impact of IVRT-based MHI on TB treatment outcomes. The study will compare treatment success at six months in participants with confirmed drug-susceptible TB randomized to the intervention and control arms. The secondary outcomes include TB cure rates in participants with pulmonary TB, appointment keeping, adherence to treatment, and attrition from care. Participants in the intervention arm will receive adherence and appointment reminders and health tips and will also have options for reporting symptoms remotely. We will also use mixed methods to determine the acceptability of the intervention, its cost-effectiveness, and its impact on TB treatment outcomes.

This study is not without justification. In 2018, there were 10 million cases of TB, with 1.45 million deaths, 250,000 of whom were patients living with HIV/AIDS (PLHIV) [1]. The disease has also harmed other health sectors [58]. However, whether MHIs can significantly contribute to a sustainable TB response is unknown. The growth of the mobile phone industry is highest in countries with weak health systems and a high burden of TB [59]. Mobile phone ownership is also high in patients with TB [19], especially among men, the population most affected by TB [1, 38]. Therefore, the delivery of the intervention at the population level is feasible.

In most LMICs, the *sine qua non* for the success of MHI is the implementation fidelity and tailoring the technology to the local context. Previous studies have demonstrated that technical difficulties are a barrier to the use and scale-up of MHIs. These include power outages and sparse network signals, especially in rural communities [33, 60]. Additionally, only 55% of Uganda is geographically covered by the Internet [24]. Thus, MHIs that have previously been demonstrated to be efficacious, including video technology [25], are not implementable in many LMICs.

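### Cure is defined by negative sputum for every bacteriologically diagnosed patient, although entry does not require a sputum-confirmed diagnosis; the rule does not measure cure in anyone confirmed on another specimen.

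*Protocol article*

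**What the plan says.** All references are to the protocol article.

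- **Trial endpoints.** Treatment success is a composite, "comprising treatment completion and cure in patients with clinically and bacteriologically diagnosed TB, respectively". For the bacteriological group, the rule reads: "In patients with bacteriologically diagnosed TB, cure is defined as having a negative sputum test in the last month of treatment". A second negative test, from any earlier time, is also required. For the clinical group, completion means six months of therapy. "The denominator for each arm will be the number of patients enrolled".
- **Inclusion criteria.** TB must be "either confirmed bacteriologically by Xpert MTB/RIF Version G4 assay" or clinically diagnosed. No specimen or disease site is named.
- **Exclusion criteria.** The only disease sites excluded are the meninges and bone or joint.
- **Study settings.** Symptomatic patients are offered sputum GeneXpert, and "those unable to expectorate are offered alternative diagnostic tests (CXR, TB LAM, sonography, tissue biopsy, CSF analysis, etc".).
- **Sensitivity analysis.** Primary and secondary quantitative endpoints are to be stratified by, among others, "TB type (pulmonary versus other forms of TB").
- **Cure population.** The Research objectives and Trial endpoints give it as microbiologically diagnosed TB. The Discussion says: "The secondary outcomes include TB cure rates in participants with pulmonary TB".
- **Follow-up tests.** Table 1 schedules sputum GeneXpert at months 0, 5 and 6. Data collection provides chest radiographs for judging cure in clinical TB only.

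**The concern.** A negative sputum test shows response only in a patient whose sputum was positive to begin with. The endpoint rule divides patients by how the diagnosis was made (bacteriological or clinical), not by whether sputum was positive. Nothing in the eligibility criteria makes those two divisions the same.

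If they differ, some participants have a primary outcome that depends on the specimen used at diagnosis and on whether they can expectorate. These participants stay in the denominator and have no second route to success. The same problem reaches the cure-only secondary endpoint and the pulmonary-versus-other stratum. The cure endpoint could also be reported on either of two populations, depending on which section the analyst follows.

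**Working it through.** **Step 1. Apply the rule to each kind of participant.**

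| Diagnosis at entry | Scored on | Does the rule measure the outcome? |
|---|---|---|
| Xpert-positive on sputum | two negative sputum tests, one in the last month | Yes |
| Clinically diagnosed, any site | six months of therapy | Yes, as completion |
| Xpert-positive on another specimen, sputum never positive, samples given | two negative sputum tests | No; negatives were expected from the start |
| Xpert-positive on another specimen, no sputum produced | two negative sputum tests | No; cure cannot be met, so non-success |

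The last two rows follow from three statements in Trial endpoints: the sputum rule covers the whole bacteriological group, completion counts only for the clinical group, and everyone enrolled is in the denominator.

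**Step 2. Does the document admit the last two rows?** The Inclusion criteria do not tie Xpert to sputum. The Exclusion criteria leave other extrapulmonary forms eligible. The Sensitivity analysis expects non-pulmonary TB, and the cure and completion model under Analysis of quantitative endpoints adjusts for TB site. So these participants are permitted. No section says how many there are, or states that Xpert is run on a non-sputum specimen.

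**Step 3. Cure population.** Microbiologically diagnosed TB (Research objectives, Trial endpoints) and pulmonary TB (Discussion) are different sets. A clinically diagnosed pulmonary patient belongs only to the second; a non-pulmonary patient confirmed by Xpert belongs only to the first.

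**Step 4. Illustration of size, on assumptions.** The document gives neither the affected share *f* nor a control success rate. Assume 70% versus 85%. The usual two-proportion formula (pooled variance under the null, two-sided 0.05, power 0.80) gives 120.5 per arm, and 120.5/(1 − 0.118) = 136.6. This is consistent with the stated 137 per arm, but other control rates come close too, so it does not establish 70% as the planning value. The sample size is not in dispute.

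As a worst case, let a share *f* have an outcome that is identical in both arms. The difference becomes 15 × (1 − *f*) points. With the 137 per arm that the all-enrolled denominator implies:

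| *f* | Difference (points) | Power, all *f* non-successes | Power, all *f* successes |
|---|---|---|---|
| 0 | 15.0 | 0.848 | 0.848 |
| 3% | 14.55 | 0.80 | 0.83 |
| 12% | 13.2 | 0.65 | 0.79 |

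The 3% and 12% come from assuming that 60% to 80% of participants are bacteriologically diagnosed and that 5% to 15% of those are confirmed on a non-sputum specimen (0.60 × 0.05 = 0.03; 0.80 × 0.15 = 0.12). None of these shares is in the document.

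**The case against.** The strongest reply is that the affected group may be nearly empty. Wherever the article names a specimen for Xpert, it is sputum (Study settings, Table 1). The alternative tests listed for patients who cannot expectorate are not described as Xpert tests. A patient positive only on LAM, imaging or histology may therefore be classed as clinically diagnosed and scored on completion already. CSF-confirmed disease would largely be meningitis, which is excluded. This stands as a limit on the size. It does not repair the rule, which contains no exception if such a patient is enrolled.

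A reader might infer that these patients' outcomes are fixed and carry no information on the intervention. The document does not support that. Two negative samples, one in the last month, require the patient to be alive, in care and attending, and retention and appointment keeping are what the reminders target. The outcome can therefore still differ between arms, but as a measure of attendance and sample submission rather than of cure.

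A reader might also infer that the whole non-pulmonary stratum is an artefact of the specimen. That goes too far, because clinically diagnosed non-pulmonary patients are scored on completion.

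The Discussion sentence is a recap, and the objectives and endpoints agree with each other. This makes the conflict minor, though it still needs correcting. Finally, the article condenses a full protocol that is not shown. That would excuse a missing detail, but here the primary endpoint rule is stated outright and has the wrong scope.

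**Conclusion.** The point holds as a defect in the endpoint definition. Read literally, the rule gives an invalid cure outcome for any participant confirmed bacteriologically on a non-sputum specimen, and the cure population is described in two ways.

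The number affected is unknown and may be small. Randomisation should make any misclassification similar between arms, so the expected effect is some dilution of the difference. The exception is that the intervention may change attendance and sample submission, so the effect need not be pure dilution.

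The power figures above should not be read as the trial's loss of power. They rest on an assumed affected share, an assumed 70% control rate and a worst case in which the outcome cannot differ between arms. No specific power loss can be derived from the document.

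**What to change.** In Trial endpoints, limit sputum-defined cure to participants with a positive baseline sputum test, and score all other participants on treatment completion. Use the same cure population in the Research objectives and in the Discussion.

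No new data are needed: method of diagnosis, site of infection and sputum GeneXpert are already collected at baseline.

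There are two costs. The cure-only analysis set becomes slightly smaller. The change also alters a primary endpoint definition in an open-label trial that had enrolled 123 of 274 participants by May 15, 2021, so it needs scientific advisory board review and approval from both ethics and regulatory bodies. It should be made and dated before any unblinded analysis.
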